### Participants, interventions and outcomes

#### Study setting

To assess the potential value of capacity building by training GPs in Tunis and Sousse using an adaptation of the mhGAP-IG (version 1.0), a cluster randomized controlled trial (RCT) with two arms (i.e., intervention and control) will be conducted. Tunis and Sousse have been chosen as they regroup the majority of the Tunisian population; they have access to the only standing mental health hospital in the country, as well as psychiatric units located in general hospitals; and in this area, there are substantially more resources allocated to mental healthcare (i.e., doctors, clinics, medication) than in other areas of Tunisia. Delegations (i.e., designated areas within the governorates) have been chosen as the clusters for this trial, seeing as health services are organized accordingly in Tunisia. There are 22 delegations in Tunis and 16 in Sousse, for a total of 38 delegations.

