#### Sample size

This trial will answer a number of important questions regarding study design, namely: What is the estimated effect size and ICC of a mental health training based on the mhGAP-IG? These parameters, to our knowledge, were not available at the time this protocol was written and defended (June 2015), and will thus make significant contribution to knowledge on the mhGAP-IG.

Following consultation with members of the Ministry of Health in Tunisia, the recommended average number of GPs to be recruited in the cluster (i.e., the delegation, many of which comprise the governorate) was suggested to be 15. While some studies using a cluster RCT to evaluate the effectiveness of a mental health training program offered to GPs in HICs do not report attrition [49–51], we are concerned that the evidence does not reflect the sampling realities in LMICs. For this reason, we aim to recruit 19 GPs per delegation, to be sure we account for a maximum of 20% attrition rate per cluster [52, 53]. Table 1 highlights the estimated sample size and number of clusters for the trial.

**Table 1 Tab1:** The sample size and number of clusters in the trial

PARAMETERS	#
n (total number of GPs)	722
# clusters (delegation)	38
n cluster (GPs on average per cluster)	19

Using the statistical software G*Power 3.1, the effect size can be calculated after data collection. Parameters will be set at: 1) test family: *t* test; 2) statistical test: difference between two independent means; 3) tail(s): two-tailed test; 4) type of power analysis: sensitivity; 5) alpha: 0.05; 6) power: 0.80; and 7) sample size (i.e., the total number of GPs) for control and intervention groups used in this trial. Once the effect size is found, the estimated ICC can be generated using the following formula, designed for cluster RCTs: *N =* N_sg_ (1 + (m-1) ICC), where:
*N =* number of participants in the trial (i.e., the total number of GPs);N_sg_ = number of participants in the trial, without considering clusters;m = number of participants in the cluster (i.e., the average number of GPs in the cluster);ICC = intra-cluster correlation (i.e., the correlation among GPs in the cluster).

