#### Statistical methods

All participants will be included in the analysis. This type of analysis is called intention-to-treat and is considered the best way to preserve the effects of randomization [53, 60]. Answers generated by questionnaires and surveys will be analyzed using SPSS Statistical Software (version 24).

T-tests on the difference in cluster means between the intervention and control groups [53] will be assessed for the questionnaires administered to the GPs. Two-tailed P values of less than 0.05 will be considered statistically significant. While the aforementioned t-tests take into account cluster level analysis, individual level analysis is discarded, which can underestimate the power of the analysis and generate misleading conclusions about the intervention [53, 61]. Adjustments can be made to the t-tests in order to account for individual level analysis. Campbell et al. (2000) [61] suggest that the t-test values (i.e., the differences between groups) should be divided by the square root of the design effect (i.e., 1 + (m-1) ICC). Two-tailed P values of less than 0.05 will be considered statistically significant. Individual level analysis will result in a higher significance level, compared with cluster level analysis [61].

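### The protocol says without condition that the adjusted individual-level t-test will be more significant than the delegation-level test; with equal delegation sizes the two t values coincide, and the reference degrees of freedom need fixing at 36

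*Protocol article*

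**What the plan says.** The Statistical methods section compares the arms by t-tests on delegation means, two-sided at 0.05. It then warns that in this analysis "individual level analysis is discarded, which can underestimate the power of the analysis and generate misleading conclusions about the intervention". As a remedy it allows an individual-level t-test whose t value is scaled down by √(1 + (m − 1)ICC), again two-sided at 0.05. It closes with "Individual level analysis will result in a higher significance level, compared with cluster level analysis". Degrees of freedom are given for neither test.

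The number of clusters is in Study setting: "There are 22 delegations in Tunis and 16 in Sousse, for a total of 38 delegations". The Sample size section and its Table 1 give the cluster size only as an average: 19 GPs recruited per delegation, against a recommended 15.

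**The concern.** The closing sentence promises a smaller p-value from the same data once GPs are the unit of analysis. The design-effect correction exists to remove the excess precision that comes from treating GPs as independent. Once it has done so, no hidden information should be left to recover, at least when delegations are of equal size. If a smaller p-value still appears, its source has to be found.

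What is at stake is the type I error. An analyst who expects the corrected individual-level test to be the more significant one has no reason to question a reference distribution that counts GPs rather than delegations. The less conservative p-value could then be reported as the more informative one.

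**Working it through.** **Inputs**
- Delegations: "for a total of 38 delegations" (Study setting). With two arms, df = 38 − 2 = 36.
- GPs per delegation: "we aim to recruit 19 GPs per delegation", where the recommended average "was suggested to be 15" (Sample size).
- Attrition: to "account for a maximum of 20% attrition rate per cluster" (Sample size).
- Alpha: 0.05, two-sided (Statistical methods).
- Assumptions, because the protocol gives no figure: ICC 0.01 to 0.20; 19 delegations per arm. A 25:13 split was also tried at ICC 0.05.

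**The plan's own figure.** 15/0.8 = 18.75, rounded up to 19, and 38 × 19 = 722 as in Table 1. With 15 remaining per delegation, 38 × 15 = 570. GP-based df would be 722 − 2 = 720 or 570 − 2 = 568.

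**Algebra for equal delegation size m.** Let MSB be the between-delegation mean square within arms and MSW the within-delegation mean square.
1. Between-delegation variance = (MSB − MSW)/m, so total variance = [MSB + (m − 1)MSW]/m.
2. ICC = (MSB − MSW)/[MSB + (m − 1)MSW].
3. Design effect = 1 + (m − 1)ICC = m·MSB/[MSB + (m − 1)MSW].
4. Total variance × design effect = MSB.
5. The corrected t is therefore the arm difference divided by √[MSB(1/n₁ + 1/n₀)]. Since n = m·k in each arm (k delegations), this equals the arm difference divided by √[(MSB/m)(1/k₁ + 1/k₀)]. MSB/m is the pooled variance of the delegation means, so this is the delegation-level t.

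The equality is exact with the ANOVA total variance. With the ordinary pooled SD it is very close, as the ratios below show.

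**Simulation, equal sizes (38 × 19, 20,000 runs per setting, no true effect)**

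| ICC | Median ratio, corrected t / delegation t | Rejected: delegation test, 36 df | Rejected: corrected, 36 df | Rejected: corrected, 720 df |
|---|---|---|---|---|
| 0.01 | 1.0002 | 4.9% | 4.9% | 5.6% |
| 0.05 | 1.0012 | 4.9% | 5.0% | 5.7% |
| 0.10 | 1.0024 | 4.8% | 4.8% | 5.6% |
| 0.20 | 1.0049 | 4.9% | 5.0% | 5.8% |

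The ICC estimate is not truncated at zero here. With truncation, the 720-df rate at ICC 0.01 is 4.9%, and the other rows hardly change. The 25:13 split at ICC 0.05 gives a median ratio of 1.0012 and 5.8% rejection on 720 df.

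**Effect of the reference distribution alone**
- Critical values: t(0.975; 36) = 2.028; t(0.975; 568) = 1.964; t(0.975; 720) = 1.963.
- P(|t₃₆| > 1.964) = 0.0573; P(|t₃₆| > 1.963) = 0.0574.
- At t = 2.00: P = 0.053 on 36 df, 0.046 on 568 or 720 df.
- An effect with 80.0% power on 36 df shows 81.7% nominal power on 720 df. That 1.7-point gain is paid for by the excess type I error.

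**Simulation, unequal sizes (illustrative: 5 to 38 GPs per delegation, mean 20)**

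| ICC | Power: delegation test, 36 df | Power: corrected, 36 df | Null: delegation test, 36 df | Null: corrected, 36 df | Null: corrected, GP df |
|---|---|---|---|---|---|
| 0.01 | 74.3% | 81.3% | 5.2% | 5.4% | 6.2% |
| 0.05 | 78.5% | 82.0% | 5.2% | 6.1% | 7.0% |
| 0.10 | 81.0% | 82.8% | 5.1% | 6.5% | 7.2% |
| 0.20 | 82.9% | 83.1% | 5.1% | 6.6% | 7.5% |

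At ICC 0.01 the gain on 36 df is largely real, because the null rates are close. It fades as the ICC grows, and part of what remains reflects a null rate above 5%, since a design effect built on the average m is then too small.

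**The case against.** The strongest reply is that equal delegation sizes are not promised. The protocol speaks of averages, GPs are volunteers found by local clinicians, and attrition may differ between delegations. Weighting by GP can then recover real power over unweighted delegation means when the ICC is small. This stands. A reader might infer that the promised gain comes only from counting GPs as degrees of freedom, or that the statement about underestimated power is false. The documents support neither: that statement says only that power *can* be underestimated, which is right for unequal sizes.

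A reader might also infer that the plan uses the wrong degrees of freedom. It does not say so. GP-based df are an inference, and a separate analysis plan may settle them. Nor does the section name the corrected test as the deciding one, and it plans P values rather than confidence intervals, so no harm to intervals can be charged to it.

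The equality of the two t values also needs an ANOVA ICC from the trial data. The Sample size section describes a different route, a back-calculation from a sensitivity analysis, and an ICC from there would break the equality. Any difference in p-value would then have another cause, but the unconditional promise would be no better founded.

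Finally, the contested wording is loose. The preceding sentence on power favours reading it as more significant, though not with certainty.

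None of this rescues a statement that the individual-level result *will* be more significant whatever the sizes and the ICC.

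**Conclusion.** The concern holds as a minor point. The unconditional sentence is wrong as a general property: with equal delegation sizes and an ANOVA ICC from the trial data, the corrected test reproduces the delegation-level result, and the only systematic source of a smaller p-value is a reference distribution based on GPs. If that were used, the true size would be about 5.7% instead of 5%, enough to move a borderline result (t = 2.00) across the threshold but little more.

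With unequal sizes the promise is partly true at small ICC and nearly empty at ICC 0.20. In the illustrative unequal-size runs, GP-based df with the average m gave 6.2% to 7.5% rejection under the null, so stating the degrees of freedom is worthwhile in either case.

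These figures rest on 38 delegations, an assumed ICC range of 0.01 to 0.20, an assumed 19:19 split and assumed unequal sizes.

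**What to change.** In Statistical methods:
- Remove the sentence that individual-level analysis will be more significant, or make it conditional: it may gain some power when delegation sizes differ and the ICC is small, and with equal sizes it reproduces the delegation-level result.
- Keep the warning about underestimated power, limited to unequal delegation sizes.
- State that any corrected individual-level t is referred to (number of delegations − 2) degrees of freedom, which is 36 with 38 delegations.

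The cost is two or three sentences. P values from the corrected test become slightly less favourable than they would be on GP-based degrees of freedom. No change to design or data collection is needed.

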### Phase 3: Exploring factors that influence implementation

#### Design

Multiple case study design will be used to explore how contextual factors within and across delegations (i.e., the cases) influence the successful implementation and expected outcomes of a mental health training based on the mhGAP-IG (version 1.0). According to Yin (2014) [62], case studies are most often used in order to answer ‘how’ questions, generally about situations that the researcher cannot control. Delegations are thus boundaries subject to a wider, uncontrollable context. They have been clearly established, and have specific particularities that we wish to uncover [63].

According to Yin (2014) [62], multiple case study design is based on a mix of qualitative and quantitative evidence. For this reason, multiple sources of data will be used to answer the research question, including focus groups with GPs, as well as quantitative data generated from the cluster RCT. These findings will be triangulated to develop what Yin (2014) [62] calls ‘converging lines of inquiry.’

#### Theoretical framework

An implementation model is necessary to guide the multiple case study design. There are a number of implementation models currently in use [64–69]. However, it is important to note that there is currently no consensus on constructs that make up implementation models and outcome measures [65, 69, 70]. This lack of agreement is due to the fact that implementing interventions is a multifaceted process that “involves attention to a wide array of multi-level variables related to the innovation itself, the local implementation context, and the behavioral strategies used to implement the innovation” [69].

While consensus on constructs and outcome measures to be included in implementation models has not been established, Champagne (2016) [71] regroups pre-existing implementation models to create a model for which complex and multi-faced factors and processes are taken into account. For this reason, Champagne (2016)’s [71] model will be used to develop focus group questions, as well as analyze or sort the collected data.

#### Data collection

Focus groups with the trained GPs working in delegations assigned to the intervention group will be conducted to explore how contextual factors influence the successful implementation of the mental health training based on the mhGAP-IG (version 1.0) and impact desired outcomes. Seven to 10 trained GPs from the intervention group will be interviewed at a time, a number that has been said to facilitate discussion by all participants [63]. Therefore, 2 focus groups will be conducted, with a total of 14 to 20 trained GPs. Focus groups will be conducted in French by JS and audio recorded. Data will be collected at T-2 (post-intervention group training).

#### Data analysis

Focus group audio recordings will be transcribed by JS and analyzed using thematic analysis [72]. This type of analysis focuses on developing common themes that are represented in the data. Important to note is that multiple case study design allows for the development of themes within cases and cross-cases [62]. More specifically, themes developed within delegations that receive the training will be reported, and they will be compared cross-delegations.

According to Padgett et al. (2008) [72], there are varied approaches to thematic analysis. The preferred method for this trial is to generate themes from the data that reflect initial interview questions, consistent with practices in evaluation research [72, 73]. In other words, the interview guide developed from Champagne (2016)’s [71] implementation model will serve as a thematic template for coding, and will be used to develop a code book before the coding process begins [72]. Coding will be done in QDA miner software (version 4.1.27).

To ensure rigor in the data analysis process, the code book will be devolved by JS, and validated by FC, NL and MP. Independent coding will be done in QDA minor software (version 4.1.27), using the developed code book. Coding from two independent reviewers will be merged, generating a percentage score for inter-rater reliability.

## Discussion

The purpose of this trial is to implement and evaluate a training based on the mhGAP-IG (version 1.0) offered to GPs in 2 Tunisian governorates (i.e., Tunis and Sousse), in order to uncover important information regarding implementation process and study design. Generated information will aid in country-wide implementation and evaluation. This training comes at an opportune time, given that Tunisia is currently undergoing a health services reform, one of its main objectives being to further develop proximity health services to address the mental health treatment gap in the country [41, 42]. In addition, given the political unrest and economic hardships currently experienced in Tunisia, mental health issues are of great national concern. While Tunisia has a mental health system, the uneven distribution of services and deficits in training for staff cause significant barriers to accessible care [41, 43].

This trial makes several practical contributions. First, its main focus is to train GPs in the detection, treatment and management of patients consulting for specific mental health problems in Tunis or Sousse, given their often limited capacity to address mental illness. Involvement of members of the Tunisian Ministry of Health in the implementation of this training program has prompted its inclusion under the national mandate of the Committee for Mental Health Promotion in Tunisia. A training under this Committee’s leadership has been dormant for years. In addition, this training aims to help further integrate mental health into primary care by training non-specialists in mental health. With GPs playing such an important role in the healthcare system, this training will help better utilize available resources in the country in order to target the mental health treatment gap.

This trial makes several contributions to the literature. To our knowledge, this is the first attempt to evaluate a mental health training program using a RCT design in Tunisia; implement a training based on the mhGAP-IG in Tunisia; and one of the first attempts to implement and evaluate a training based on the mhGAP-IG in a French-speaking nation. The trial will thus help build research capacity in Tunisia and more generally in LMICs, currently under-represented in the mental health literature [7, 34]. This trial also compliments the effectiveness results with implementation analysis, a current priority in global mental health [7, 26, 34]. Acknowledging factors that influence the successful implementation of a training program generates understanding on how context, especially within a health services reform such as the one currently underway in Tunisia, influences desired outcomes [36].

Lessons learned from this trial (i.e., successes and challenges regarding implementation of the training and acceptability of the trial design) can also be of use to other LMICs interested in implementing and evaluating a mental health training program based on the mhGAP-IG; designing a cluster RCT to evaluate the mhGAP-IG; or exploring contextual factors that can influence the success of a training intervention and expected results in a low-resource setting.

## Abbreviations

EPHPP: Effective public health practice project
GPs: General practitioners
HICs: High-Income countries
ICC: Intra-Cluster correlation
IG: Intervention guide
LMICs: Low- and middle-income countries
mhGAP: Mental health gap action programme
mhGAP-IG: Mental health gap action programme intervention guide
RCT: Randomized controlled trial
PAHO: Pan-American Health Organization
WHO: World health organization
